### 7.3.2. Co-primary endpoint: MDRB eradication

The significance of the difference of prevalence between final (f), deterioration time (d) and baseline time (b) will be assessed a paired t-test. As for the main endpoint, Log transformed values will be used in case the MDRB is distributed according a Log-Normal distribution.

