## 3. OBJECTIVES

### ➤ Co-primary objectives:

- Efficacy of AFMT in dysbiosis correction in AML or HR MDS patients undergoing chemotherapy and antibiotherapy
- Efficacy of AFMT in MDRB eradication

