#### **5.2. Exclusion criteria**

- Acute promyelocytic leukemia (AML-M3)
- Known allergy or intolerance to trehalose or maltodextrin
- Pregnancy: positive urinary or blood test in female of childbearing potential
- Severe disease with a life expectancy  $< 3$  months
- Other on-going interventional protocol that might interfere with the study
- Non eligibility for collection of autologous stools upon admission:
  - Patients refusing to consent
  - Antibiotherapy at the time of study inclusion  $\geq 4$  days
  - Concomitant or previous diagnosis of a significant inflammatory bowel disease (UC, CD) or other progressive digestive disease requesting treatment or further medical exploration

|                                                                                                         |                      |                                                                                               |
|---------------------------------------------------------------------------------------------------------|----------------------|-----------------------------------------------------------------------------------------------|
| [figure not shown]
MaaT Pharma | Protocol             | Protocol N°: MPOH02
EudraCT N° : 2015-004335-12
Version 10.0
Date : 20 November 2017 |
|                                                                                                         | ODYSSEE STUDY |                                                                                               |

- Presence of severe colitis of any etiology at the time of admission or severe digestive disorders (acute or chronic diarrhea) within 3 months preceding inclusion
- Presence of blood in faeces collected at the time of inclusion
- Patient getting a recent colonoscopy (within 3 months preceding inclusion)
- Detection of MDRB, pathogenic bacteria, parasites, norovirus and/or rotavirus during screening of autologous stool collected immediately after the inclusion visit
- Non eligibility for inoculum transplantation: persistent mucositis, colitis, or haemorrhoids, presence of blood in more than 1 patient's faeces out of 3 the week preceding the transplantation
- Non feasibility of inoculum procedure: patient refusal; technical or biological mismatch of the inoculum
- Absence of effective contraceptive method for female of childbearing potential
- Lactation
- Inability to give an informed consent

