***D29 (between D24 and D34, depending on patient’s condition) – Visit 2 – Faeces analysis for dysbiosis characterization***

After aplasia completion ,faeces and blood will be collected by caregivers within 3 days before antibiotics discontinuation (around Day 29) (**Procedures will be provided by BIOFORTIS SAS**) for biochemical assay, bacteriology (detection of MDRB and *C. difficile*), determination of dysbiosis using metagenomic analysis and analysis of blood immune cells. Detection of MDRB and/or *C. difficile* will not constitute a criterion for exclusion but will allow the measure of the potential impact of chemotherapy and antibiotherapy on the emergence of these bacteria. The patient will fulfil the EQ-5D-5L questionnaire to evaluate its gastrointestinal symptoms and its quality of life. The patient is next prepared for the following AFMT according to the procedure (**Appendix 1**).

|                                                                                                         |                      |                                                                                               |
|---------------------------------------------------------------------------------------------------------|----------------------|-----------------------------------------------------------------------------------------------|
| [figure not shown]
MaaT Pharma | Protocol             | Protocol N°: MPOH02
EudraCT N° : 2015-004335-12
Version 10.0
Date : 20 November 2017 |
|                                                                                                         | ODYSSEE STUDY |                                                                                               |

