#### 7.1.2. Evaluation of AFMT efficacy in MDRB eradication

Based on bacterial culture and analysis of resistance gene expression by metagenomics, we will evaluate the prevalence and the quantity of MDRB before (D0), after chemotherapy/antibiotherapy (D29) and after AFMT (D40).

Prevalence of MDRB will be compared between D40 and D29 to evaluate AFMT efficacy in MDRB eradication.

---

All documentation of **MaaT Pharma** is PROPRIETARY information and may not be forwarded to third parties without prior written consent from **MaaT Pharma**. Reproductions, either in part or in whole, may not be published or copied in any manner, without the explicit written consent of **MaaT Pharma**

|                                                                                   |                      |                                                                                               |
|-----------------------------------------------------------------------------------|----------------------|-----------------------------------------------------------------------------------------------|
| [figure not shown] | Protocol             | Protocol N°: MPOH02
EudraCT N° : 2015-004335-12
Version 10.0
Date : 20 November 2017 |
|                                                                                   | ODYSSEE STUDY |                                                                                               |

Further to recruitment difficulties, the company would limit the number of cases. The following table provides the sample size needed for some beta values (from 0.1 until 0.25) and for some effect size (defined as the standardized mean difference). It is apparent that small values of effect sizes need at least 44 patients (for effect size=0.4). However, when the effect size is at least 0.6 and with a beta risk of at least 0.20, 20 patients should constitute an acceptable size.

| Effect Size | Power= | 0.1   | 0.15  | 0.20  | 0.25  |
|-------------|--------|-------|-------|-------|-------|
| 0.4         |        | 66.00 | 57.00 | 49.00 | 44.00 |
| 0.5         |        | 43.00 | 36.00 | 32.00 | 28.00 |
| 0.6         |        | 30.00 | 25.00 | 22.00 | 20.00 |
| 0.7         |        | 22.00 | 19.00 | 16.00 | 15.00 |
| 0.8         |        | 17.00 | 15.00 | 13.00 | 11.00 |
| 0.9         |        | 13.00 | 12.00 | 10.00 | 10.00 |
| 1           |        | 11.00 | 10.00 | 9.00  | 8.00  |

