### Conclusion.

A sample size of 20 patients does not reduce the interest of the study, for the main endpoint (change of dysbiosis), however, the power of the secondary endpoints (including MDRB) will inevitably be reduced. The exploratory feature of this study does allow this relaxed value, and alpha value can be increased (or one-tailed tests should be used) to increase power.

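### Section 7.3.2 tests sparse yes/no MDRB carriage by paired t-tests at three times. With 3–4 clearances the p-value is about a third of the exact one, and tests against D0 cannot show eradication.

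*Protocol*

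**What the plan says.** All references are to the Protocol.

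- **Test (7.3.2).** "The significance of the difference of prevalence between final (f), deterioration time (d) and baseline time (b) will be assessed a paired t-test". The next sentence adds: "As for the main endpoint, Log transformed values will be used in case the MDRB is distributed according a Log-Normal distribution".
- **Measure (7.1.2).** MDRB is assessed in two forms: "we will evaluate the prevalence and the quantity of MDRB before (D0), after chemotherapy/antibiotherapy (D29) and after AFMT (D40").
- **Efficacy comparison (7.1.2).** "Prevalence of MDRB will be compared between D40 and D29 to evaluate AFMT efficacy in MDRB eradication". The baseline is not part of it.
- **Baseline selection (5.2).** An exclusion criterion reads: "Detection of MDRB, pathogenic bacteria, parasites, norovirus and/or rotavirus during screening of autologous stool collected immediately after the inclusion visit". Section 6.4.2 repeats it for the inclusion stool.
- **Purpose of the D29 detection (6.4.2, Visit 2).** It "will allow the measure of the potential impact of chemotherapy and antibiotherapy on the emergence of these bacteria".
- **Expected counts (7.1.2, Related Power sample).** 20 patients, with prevalence 0.15 to 0.20 before AFMT and 0.01 to 0.05 after.
- **Status.** Section 3 lists "Efficacy of AFMT in MDRB eradication" among the co-primary objectives, and the title of 7.3.2 agrees. The conclusion of 7.1.2 says that "the power of the secondary endpoints (including MDRB) will inevitably be reduced". Section 7.2.2, under secondary endpoints, also treats MDRB as one of the health-status variables.
- **Sidedness.** None is fixed for MDRB. The conclusion of 7.1.2 leaves open a larger alpha or one-tailed tests.

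**The concern.** Prevalence at two visits in the same patients is a paired binary outcome. All the information on change lies in the discordant patients, those who clear or acquire carriage between visits. With three or four of them, a t-test on differences of −1, 0 and +1 relies on an approximation with very little beneath it. Eradication could be declared significant on a handful of patients where an exact paired test would not reach 0.05.

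The three-time comparison adds a second problem. Every transplanted patient is screen-negative at D0, so the change from D0 to D29 or D40 can only be zero or upward. Its direction is set by selection, and neither contrast measures clearance.

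Finally, 7.1.2 and 7.3.2 name different comparisons, and the document gives MDRB two ranks. A reader cannot tell which test answers the objective, or whether that test counts towards trial success.

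**Working it through.** **Inputs.** n = 20. D29 prevalence of 0.15 to 0.20 gives 20 × 0.15 = 3 to 20 × 0.20 = 4 carriers. D40 prevalence is 0.01 at the favourable end. Alpha of 0.05 is an assumption, because the Protocol fixes none for MDRB; both sidednesses are shown.

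**The plan's own figure.** The power table labelled for 20 patients gives 0.729 for 0.20 to 0.01. An arcsine calculation for two independent groups of 20, two-sided, gives 0.633. The same formula with 25 per group gives 0.729 and reproduces the whole table to within 0.0011. The table therefore fits neither n = 20 nor a paired design. Only its prevalence assumptions are used here.

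**P-values when x carriers clear and none acquire.**
- Paired t: mean = x/20; variance = (x − x²/20)/19; t = mean/√(variance/20), on 19 df.
- x = 3: mean 0.15, variance 2.55/19 = 0.1342, t = 1.83.
- x = 4: mean 0.20, variance 3.2/19 = 0.1684, t = 2.18.
- Exact McNemar: one-sided p = 0.5^x, two-sided twice that. Mid-p, one-sided: half of 0.5^x.

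| Cleared | t, one-sided | Exact, one-sided | Mid-p, one-sided | t, two-sided | Exact, two-sided |
|---|---|---|---|---|---|
| 3 | 0.041 | 0.125 | 0.0625 | 0.083 | 0.250 |
| 4 | 0.021 | 0.0625 | 0.031 | 0.042 | 0.125 |

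Ratios of t to exact: 0.041/0.125 = 0.33 and 0.021/0.0625 = 0.34. The exact test first reaches 0.05 at 5 clearances one-sided (0.5^5 = 0.031) and at 6 two-sided (2 × 0.5^6 = 0.031).

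**Type I error of the t-test under no change (all tables enumerated, n = 20).**
- Averaged over all tables, one-sided: 3.1%, 4.7%, 5.2% and 5.0% at discordance rates of 10%, 15%, 20% and 25%.
- Averaged over all tables, two-sided: 1.4%, 3.1%, 4.4% and 4.9% at the same rates.
- Given exactly 3 discordant patients: 12.5% one-sided, 0% two-sided.
- Given exactly 4: 6.25% one-sided, 12.5% two-sided.

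**Power, one-sided 0.05, no acquisitions.** Clearance probability is 0.20 − 0.01 = 0.19, or 0.15 − 0.01 = 0.14.

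| Change | Paired t | Mid-p McNemar | Exact McNemar |
|---|---|---|---|
| 20% to 1% | 0.76 | 0.54 | 0.33 |
| 15% to 1% | 0.54 | 0.30 | 0.14 |

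**D0 contrast.** With every D0 value at zero, 4 acquisitions of 20 by D29 give a two-sided t p-value of 0.042 against an exact 0.125. The informative summary is the acquisition proportion, 4/20 = 20%, with Clopper-Pearson interval 5.7% to 43.7%.

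**Clearance among carriers.** If all x carriers clear, the lower 95% Clopper-Pearson limit is 0.025^(1/x): 29% for 3/3 and 40% for 4/4. These limits show how little three or four patients can establish.

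**The case against.** **A reader might infer that the paired t-test is invalid or grossly liberal.** The enumeration does not support that. Its average one-sided error is about 3–5% at plausible discordance. The 12.5% and 6.25% rates arise only after conditioning on 3 or 4 discordant patients. Part of the gap is also the conservatism of exact McNemar, whose one-sided size is only 0.4% at 15% discordance and 0.9% at 20%. Mid-p would call 4 of 20 significant one-sided (0.031). What stands is that the p-value printed for the expected tables conveys more evidence than an exact paired analysis does. With 3 clearances, only the one-sided t-test crosses 0.05.

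**A reader might infer that 7.3.2 log-transforms a 0/1 variable.** The sentence is conditional, and 7.1.2 also measures quantity, so it can be read as referring to load. What stands is that it follows a sentence about prevalence without saying so, and gives no rule for zeros.

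**A reader might infer that the D0 comparison is meaningless.** Section 6.4.2 gives D29 detection a purpose, emergence under treatment. Zero at D0 also applies only to the screening tests, not to metagenomic resistance-gene quantity. What stands is that a significance test against a screened zero says nothing about eradication.

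**A reader might infer a 9.75% family error from two co-primary tests (1 − 0.95²).** That needs independent tests and a rule that either one suffices. The Protocol states no such rule; if both must succeed, there is no inflation.

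The study is also exploratory, and 7.1.2 concedes low MDRB power. That tempers the consequences but does not reconcile the sections.

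**Conclusion.** The point holds as a defect of specification. Section 7.3.2 fixes a test poorly suited to about 3–4 expected carriers of 20, extends it to baseline contrasts whose direction is set by exclusion, departs from the comparison in 7.1.2, and leaves MDRB both co-primary and secondary. The effect is a p-value about one third of the exact paired value at the expected counts, not a large average type I inflation. The figures assume 20 evaluable pairs, the Protocol's 15–20% carriage at D29, complete clearance with no acquisitions in the p-value examples, and alpha 0.05. Acquisitions between D29 and D40 would change the p-values and powers. The documents support asking for one consistent status for MDRB; they do not settle which status is right.

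**What to change.** In 7.3.2:

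- Test MDRB prevalence for D40 versus D29 only, matching 7.1.2, with a McNemar test. State exact or mid-p, and the sidedness.
- Lead with the number and proportion cleared among D29 carriers and its Clopper-Pearson interval.
- Report emergence from D0 to D29 as an acquisition proportion with an exact interval, replacing the significance tests against D0.
- Restrict the log transform to quantitative MDRB load, with a stated rule for zeros.

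Reconcile section 3 and 7.3.2 with the conclusion of 7.1.2. If MDRB stays co-primary, say whether success needs both endpoints or either.

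The change is wording, with no new data. Its price is power: for 20% to 1%, one-sided, from 0.76 to 0.54 with mid-p or 0.33 with exact McNemar. The exact version cannot reach one-sided 0.05 with fewer than 5 clearances, so at the expected 3–4 carriers it could not succeed. That should be stated openly, and it is the reason to put estimation first.

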### 7.3.3. Secondary analyses : Association between S and health status

The assumed hypothesis is that the deterioration of the microbiota (MB) is associated with patient health status. In what follows, we consider one variable H in particular among the candidate HSR set, with  $H_b$ ,  $H_d$  and  $H_f$  designating the three values measured at baseline, deterioration and final times, respectively. Let us consider the following model:

$$H_i = k_0 + k_b.H_{i-1} + k_c.S_i + \eta_{i,\text{center}} \quad \text{for } i=b,d,t \quad [1]$$

|                                                                                                         |                      |                                                                                               |
|---------------------------------------------------------------------------------------------------------|----------------------|-----------------------------------------------------------------------------------------------|
| [figure not shown]
MaaT Pharma | Protocol             | Protocol N°: MPOH02
EudraCT N° : 2015-004335-12
Version 10.0
Date : 20 November 2017 |
|                                                                                                         | ODYSSEE STUDY |                                                                                               |

This model is a mixed model by considering the 3 measurements correlated within the patient random factor. The estimates are  $k_0$ ,  $k_b$ ,  $k_c$ , and the standard deviation  $\eta$ . This model assumes the instantaneous association between the MB diversity  $S$  and the health status, and tests the existence of an association between  $H$  and  $S$ , however, without possibility to test either relationship  $H \rightarrow S$  or  $S \rightarrow H$ .

However, this model can be tested in two different ways:

$$H_{i+1} = k_0 + k_b.H_i + k_c.S_i + \eta.\text{center} \quad \text{where for } i=b,d,t \quad [2]$$

In this model [2], health status (HS) at time  $(i+1)$  is assumed dependent on MB diversity at time  $i$ . This model will test the effect of MB diversity as a directional effect of lag=1 on HS, in other words, MB status affects HS with some delay, such result providing some evidence of a causal effect of MB on HS.

Another formulation should be

$$S_i = k_0 + k_b.S_{i-1} + k_c.H_{i-1} + \eta.\text{center} \quad \text{where for } i=b,d,t \quad [3]$$

In this model [3], health status at time  $(i)$  is assumed to affect MB diversity at time  $i+1$ . This model will test the effect of HS effect as a directional effect of lag=1 on MB diversity. In other words, HS status affects MB with some delay, such result providing some evidence of a causal effect of  $HS \rightarrow MB$ .

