## 7. STATISTICAL CONSIDERATIONS

### 7.1. Main endpoints

#### 7.1.1. Evaluation of AFMT efficacy in dysbiosis correction

The microbiota diversity will be measured by the Simpson diversity index (S). S will be calculated at the three main times D0, D30 and D40 corresponding respectively to baseline (Sb, before antibiotherapy and chemotherapy), post-treatment (Sd, dysbiosis maximum deterioration post-antibiotherapy) and final value post-AFMT (Sf). Our hypothesis is that after an expected deterioration due to chemotherapy, the microbiota diversity should return to its baseline Sb after AFMT (thus  $Sf/Sb = 1$ ). To simplify the models, we related diversity at deterioration and final values to their ratio on baseline. In what follows, Sd and Sf denote the dimensionless ratios Sd/Sb and Sf/Sb respectively.

As Simpson index constitutes a particular way at measuring microbiota, other indexes of diversity (Shannon) and germs repartition (Bray-Curtis, Sorensen, Pearson, or Spearman indexes) will be calculated.

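### Association models [1]–[3] have no visit term, so a shared chemotherapy time course can appear as a microbiota–health link, which [2] and [3] would read as causal

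*Protocol*

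**What the plan says.** Section 7.3.3 considers one health variable H, chosen from a wide set of candidates, with values at baseline (b), deterioration (d) and final (f). Model [1] is "H_i = k_0 + k_b.H_{i-1} + k_c.S_i" plus a centre term. Model [2] is "H_{i+1} = k_0 + k_b.H_i + k_c.S_i" plus centre. Model [3] regresses S on the previous S and the previous H, plus centre. The text adds a patient random factor: "This model is a mixed model by considering the 3 measurements correlated within the patient random factor". None of the equations contains visit or time, and the index is given as b, d, t for all three.

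The interpretation differs by model. For [1] the section claims association only, "without possibility to test either relationship" between H and S. For [2] a positive result is described as "such result providing some evidence of a causal effect of MB on HS", and [3] is given the same reading from health to microbiota.

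The scale of S comes from 7.1.1: "In what follows, Sd and Sf denote the dimensionless ratios Sd/Sb and Sf/Sb respectively". The same section expects a common course in S: "Our hypothesis is that after an expected deterioration due to chemotherapy, the microbiota diversity should return to its baseline Sb after AFMT".

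**The concern.** The protocol itself describes a common cause. Sections 1.4 and 2 say that intensive chemotherapy and broad-spectrum antibiotics during aplasia disturb the microbiota and accompany a high infection risk. A health variable driven by the same treatment will move with S from visit to visit whether or not diversity affects health. With no visit term, the model cannot separate that shared movement from a patient-level link.

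The ratio scale adds a second difficulty in [2]. Baseline S is either Sb/Sb = 1 for every patient or, if left raw, on a different scale from Sd and Sf. In the first case the baseline row holds no between-patient information on S.

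The effect of dysbiosis correction on clinical status is a stated secondary objective (section 3), and 7.5.1 acknowledges that the trial has no control group. An artefact of timing could therefore be reported as directional evidence.

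**Working it through.** The protocol gives no figure for 7.3.3 to reproduce, so the check is whether the printed models hold their nominal error rate.

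**Usable rows.** Only b, d and f are defined. Models [1] and [3] can use outcomes at d and f. Model [2] can use b→d and d→f. That is two rows per patient, with 20 patients (6.3).

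**Why S is close to a visit indicator in [2].** Assume ratio means of 1 at b and 0.4 at d, with SD 0 and 0.2.
- Variance of S between the two rows: ((1 − 0.4)/2)² = 0.09.
- Average variance within rows: (0 + 0.2²)/2 = 0.02.
- Correlation of S with visit: √(0.09/0.11) = 0.90. Simulated: about 0.90–0.93.

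**What the coefficient then measures.** Let H fall by 1 SD at d and recover at f, with no link to S. Ignoring the lagged-H term, covariance = (1 − 0.4)(−1 − 0)/4 = −0.15, so the slope is −0.15/0.11 = −1.36 (simulated with the lag term: −1.33). If H falls at f instead, the slope is +1.36 (simulated: +1.40). The sign follows the time course and says nothing about the microbiota.

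**False-positive rates.** In every simulation H and S were independent given visit, so each rejection is false. Assumed: n = 20, two-sided 5% (7.3.3 states no level), 2,000 trials per setting.

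Simulation A: mixed model with a patient random intercept, as the text states; S means 1 / 0.4 / 0.9, SD 0.2; within-patient correlation 0.4 for H and 0.5 for S; no centre effect. Entries are for shifts in H of 0.5 / 1 / 1.5 SD.

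| Course of H | [1] | [2] | [3] |
|---|---|---|---|
| Dip at d, recovery at f | 41 / 83 / 88% | 51 / 93 / 97% | 7 / 13 / 19% |
| Dip at f only | 31 / 75 / 96% | 36 / 85 / 99% | 6 / 6 / 6% |
| Dip at d, stays low | 9 / 13 / 17% | 10 / 17 / 25% | 8 / 12 / 19% |

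With no time course in H the rates are 5.8%, 6.0% and 6.2%.

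Simulation B: cluster-robust linear model, S means 1 / 0.6 / 0.9, SD 0.2 at d and f, dip and recovery in H. Model [1] gives 20 / 45 / 58% and [2] gives 30 / 68 / 87%. Model [3] was not run.

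**Which feature drives it.** Putting S on the raw scale without a visit term leaves [2] at 46 / 88 / 93% for dip and recovery. Adding a visit factor on the ratio scale gives 4.6–6.4% in [1], 4.8–6.3% in [2] and 6.7–8.6% in [3] across the settings of simulation A. With raw S and a visit factor together (no shift, or dip and recovery), the rates are 4.8–5.9%, 5.2–5.8% and 4.8–6.2%. In simulation B the visit factor brings [1] and [2] to about 8–11%, so part of the excess there belongs to that test with 20 clusters.

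**Health variables without the assumed course.**
- EQ-5D VAS means and SDs at V1–V3 from Supplementary Table 2 (61.05 (26.05), 76.24 (16.44), 78.75 (16.61)): 7% in [1], 8% in [2], 7% in [3].
- MDRB carriage, zero at baseline because carriers are excluded (5.2), assumed 20% at d and 1–20% at f: 0–5% in [1] and [2], with near-degenerate fits when few carriers remain at f; 11–13% in [3].

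**The case against.** The strongest reply is that the problem depends on which H is chosen. Worsening at D29 is an assumption. The EQ-5D VAS in Supplementary Table 2 rises from V1 to V2, and 7.2.2 names MDRB reduction as the most important health variable; neither produces material inflation in [1] or [2]. This stands, and it limits the size. It does not rescue the models, because H is left open among infectious, digestive and other variables, and some of these can be expected to track treatment.

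A reader might infer several stronger things that the documents do not support:
- *All three models are called causal.* Model [1] expressly disclaims direction, and joint movement across visits is arguably part of its stated hypothesis.
- *The ratio scale causes the inflation.* Raw S alone leaves [2] badly inflated. The separate harm of the ratio is the lost or incommensurable baseline row. That S equals 1 at baseline is implied by 7.1.1 and not written there.
- *The patient effect is missing.* The equations show only centre, but the sentence beside [1] states a patient random factor.
- *The index range is impossible for every H.* Some variables are also collected at D70 or before D0. Still, 7.3.3 defines only three values of H, and t is not one of them.

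Finally, the analysis is secondary in a trial that calls itself exploratory, and a SAP is due before analysis (7.6). This lowers the priority. But 7.3.3 writes the equations and their interpretation out and, unlike 7.2.1, defers neither to the SAP.

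**Conclusion.** The point holds in limited form. As printed, [1]–[3] cannot distinguish a microbiota–health link from a time course shared by all patients, and for [2] and [3] the protocol would describe the result as evidence of causation. For an H that dips at D29 by 0.5–1.5 SD and recovers by D40, false-positive rates are roughly 20–88% in [1], 30–97% in [2] and 7–19% in [3]. These ranges rest on the assumed course of H, the assumed means and SD of S, 20 patients and a two-sided 5% level. With the EQ-5D VAS means all three models are close to nominal (7–8%); with MDRB as simulated, [1] and [2] are not inflated and [3] is at 11–13%. It would be wrong to conclude that a false result is likely whatever H is chosen, or that the co-primary comparisons are compromised.

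**What to change.** In 7.3.3, or in the SAP with a matching correction to the protocol:

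- Add visit as a fixed factor to [1]–[3] and keep the patient random factor already stated, writing it into the equations.
- Use S on one scale, raw or log, at all visits, so that the baseline row carries information.
- Restrict the index to visits that exist: i = d, f for [1] and [3]; i = b, d for [2]. Remove the undefined t.
- Replace causal effect with lagged association in the reading of [2] and [3]. A visit factor does not make an uncontrolled association causal.

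Section 7.5.2 builds [4] and [5] on the same form and also prints no visit term, so the same line should carry over.

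The cost is one degree of freedom. Model [2] will then rest mainly on within-visit differences among 20 patients, so its power will be low; the report should say so.
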